##### Pre-treatment covariates

In order to be able to adjust for potential imbalances, across the two randomization groups, in the distributions of covariates, that may be potentially associated with the outcomes, baseline measurement of the following variables will be carried out: basic socio-demographic data including age, BMI, general health status, medical history and medications, parity and obstetrical history as well as type and duration of UI. In secondary analyses, we will then use multivariable regression models to adjust the between-groups differences in the outcomes for these covariates, in addition to the pre-treatment values of the respective outcome variable.

##### Sample size calculation

Sample size was calculated so as to ensure the adequate power and type I error rate for testing the primary hypothesis of non-inferiority of the group-based intervention relative to the individualized intervention, in achieving the relative reduction (in %) in the number of UI episodes at one year. Sample size calculations followed CONSORT Guidelines for non-Inferiority trials [68]. First, based on clinical relevance [69] (minimum clinically relevant difference = 10%) and our pilot data [18–22], we set the “margin of equivalence” (i.e. the upper limit of the non-inferiority interval) as corresponding to a 10% difference between mean % reduction in the number of UI episodes in the “standard treatment” of the individualized intervention minus the group-based intervention arm. This implies that we test the null hypothesis H0:d ≤ 10%, where d denotes the true difference between the mean relative reductions in the number of UI episode in the two arms (individualized minus group-based) against the alternative hypothesis H1:d > 10%. According to the CONSORT guidelines, this choice of the “margin of equivalence” implies that the non-inferiority hypothesis should be rejected whenever the upper bound of the two-tailed (1 – 2α)% confidence interval (CI) for the difference between the two mean % reductions exceeds 10%. In the specific context of a non-inferiority trial, α is the selected risk of a false acceptance of the non-inferiority hypothesis (based on a one-tailed CI-based test, equivalent to an independent-group t-test); i.e. of a false conclusion that a truly inferior intervention is equally efficacious as the “standard treatment” [68].

To err on the conservative side, we relied on the “standard” 95% CI, which corresponds to a stringent one-tailed type I error rate of α = 0.025 (2α = 1–0.95 = 0.05). Similar to other recent non-Inferiority trials (e.g. [70, 71]) and CONSORT guidelines [68], for the purpose of sample size calculation, we assume that the true difference between the mean reductions (%) achieved by the two interventions will be zero (i.e. that they are equally effective). Note that this assumption of equivalence of the two interventions being compared in our trial is consistent with both (a) clinical expectations and (b) (limited) published evidence concerning young and middle-aged UI women [72–74]. Finally, both published trials, which evaluated similar interventions in older women, reported within-group standard deviations (SD) of the individual % reduction scores of about 27% [44, 75]. Accordingly, we assumed SD = 27% in our calculations.

Under the above assumptions, we estimated the sample size needed to ensure high (90%) power to demonstrate the non-inferiority of the group-based intervention (assuming, as mentioned above, that the true difference is 0%). Thus, we calculated N, for which the probability that the upper boundary of the two-tailed 95% CI for the difference in the mean relative reduction (Individual – Group) excludes the “upper threshold of non-inferiority” (10% difference), will reach at least 90%. The sample size calculations were performed using the program in the PASS software package, designed specifically for power/sample size estimation for non-inferiority trials [76]. Under the assumptions outlined above, we will need 155 participants per group, for a total of 310 individuals. We also need to account for possible losses to follow-up, as we expect a 15% attrition rate by the end of the one year, based on both our pilot data and similar published trials [16, 17, 22, 51]. Thus, we will recruit an additional 54 participants per group, increasing the total number of participants to 364 (364*(1–0.15) = 310).

#### Trial management

The PI and a research coordinator regularly contact (through emails, telephone, or in person) each participating urology and gynecology clinic in order to promote and monitor progress in recruitment. The PI, the evaluators, physiotherapists, research assistant, and the Sherbrooke and Montreal coordinators conduct conference calls or face-to-face meetings in order to monitor the study’s progress. All members of the research team are kept informed of progress through a newsletter, every six months.

All collected data are anonymized and kept under lock and key at [name] and [name]’s laboratories at the research center of the Institut Universitaire de Gériatrie de Montréal and research center of the Cewntre Hospitalier de l’Université de Sherbrooke. After each assessment and on the same day, files are reviewed by the research assistant in order to identify missing data. Any missing information is retrieved immediately by research assistants directly from the study participants. Data are entered weekly – trimestrally (depending on recruitment rate) into a computerized database system *SPSS data Entry 4.0* both in Sherbrooke and in Montreal centers. The database is backed up on a weekly basis. A PIN number known only to the research group is required to access the data entry computer. A final quality-control step will be taken at the time of the data analysis by the trial statistician. Frequency distributions and ranges will be analyzed to detect outliers that could signal potential errors. The data will be analyzed without any nominative identifiers.

#### Adherence

Based on the results of our previous feasibility study and post-study focus group, no significant problems are expected with treatment adherence in either group [22, 26]. Indeed, participants (*n* = 27) in the feasibility study complied well with study demands in terms of attendance at the treatment sessions (90%), completion of the daily exercise program (78%), and data collection (95%) [26]. Post-study focus groups identified “close supervision by the physiotherapist” and a “short daily PFM exercise program” as key facilitators in the participant’s completion of a 12-week group-based PFMT program and their adherence to the daily home PFM exercise program [22]. Adherence will be measured as follows: the women will be provided with diaries to record home exercise adherence for the 12-week treatment session. In addition, exercise maintenance will be assessed with a standardized questionnaire, at three and six months post intervention as well as at the 12-month follow-up evaluation. Additionally, adherence to each supervised weekly treatment sessions will be recorded by the physiotherapists.

To ensure evaluation and treatment adherence, we used the following strategies: (1) individual consultations using vaginal digital palpation ensure that participants can perform a PFM contraction correctly (the physiotherapist is available before and after individual and group treatment sessions to provide tips and answer questions regarding the weekly treatment and home exercise program); (2) an exercise diary is given to each participant to bring home and is verified by the physiotherapist each week throughout the treatment; (3) the home exercise program comprises a short and simple daily PFM exercise program to facilitate exercise practice; (4) women in both groups are reminded of their appointments (evaluation and treatments) by a research assistant. They are scheduled at participants’ convenience; (5) follow-up contact calls are made at three and six months post intervention to maintain contact. Evaluators solicit information from participants on their intention to change address or telephone number and on the frequency of visits to incontinence-related medical professionals. They also verify if medications have been prescribed, surgery conducted, and if there are any other health problems likely to influence UI. Finally, they monitor their continued adherence to PFMT; and (6) participants are reimbursed for their travel and parking expenses related to participation in the study.

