#### Blinding

Investigators, data analysts, and physiotherapists in charge of outcome evaluations remain blinded to the individual participants trial group allocation. Although participants cannot be blinded to their own group allocation, they are blinded to the study’s hypothesis and to the treatment offered in the alternate group. Despite their different formats, both groups have parallel weekly sessions in terms of content and time, but at different locations and/or on different days. To minimize the risk of assessor’s unblinding, participants are asked (both in the consent form and at the time of each assessment) not to discuss their treatment with the independent assessor. In addition, in each center, the assessment is separated from the intervention session, by both time and location.

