##### Costs related to interventions

The DBICI, a universally applicable questionnaire, has been adapted to measure the intervention costs for the two treatment groups [41, 65]. The validated DBICI has been used in RCTs with community-dwelling populations of women aged 40 years and over for non-surgical UI interventions [66] and is recommended by the International Consultation on Incontinence Research Guidelines [10, 42]. Section 1 of the DBICI documents, monthly self-reported personal incontinence expenditures (disposable and re-usable incontinence products), is used integrally. Section 2 deals with treatment expenditures and has been adapted as follows: (1) Treatment costs: rather than self-reported, treatment duration (in h) for each participant is based on statistics maintained by the research coordinators using a standardized form developed for a previous cost-effectiveness study [67]. The number of hours is multiplied by the mean hourly salary of the physiotherapists participating in the study. For the group-based PFMT, the total number of hours will be divided by the number (n = 8) of intended class participants (i.e. not actual attendance); (2) Other consultations: the frequency of visits to incontinence-related medical professionals is documented by category (general practitioners and specialists). A research assistant will phone participants at three months and six months post intervention in order to collect information. Estimated costs are based on the frequency and a mean cost per visit based on the public health system regulations for each category (Régie de l’assurance maladie du Québec). UI medication costs is excluded from the trial as those with UI medication are excluded at study entrance.

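### The three- and six-month calls are given to two different roles, and one of them appears to be the blinded outcome assessor

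*Protocol article*

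**What the plan says.** The protocol article describes the calls in two places.

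- **Costs related to interventions:** "A research assistant will phone participants at three months and six months post intervention". The purpose given is to collect data on visits to professionals about incontinence.
- **Adherence, item (5) of the list of strategies:** "follow-up contact calls are made at three and six months post intervention to maintain contact". The next sentence reads: "Evaluators solicit information from participants on their intention to change address or telephone number", and adds how often they have seen professionals about incontinence. The text goes on: "They also verify if medications have been prescribed, surgery conducted", along with other health problems that could influence incontinence; and last, "Finally, they monitor their continued adherence to PFMT".

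The Blinding section says that "physiotherapists in charge of outcome evaluations remain blinded to the individual participants trial group allocation". As a safeguard, women are asked, in the consent form and at every assessment, not to talk about their treatment with the independent assessor.

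**The concern.** Two sections give what look like the same calls to different staff, and the choice matters for blinding. If the person who will later grade muscle strength also asks a woman how she is keeping up her training and what other care she has had, the protocol itself opens a conversation that its blinding safeguard is meant to prevent.

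At stake are the outcomes that depend on the assessor at one year: Oxford grading by palpation, dynamometry and ultrasound morphometry. Women know which treatment they received, so these measurements help to corroborate what they report themselves. In a non-inferiority trial, an assessor who has learned the allocation could shift ratings in either direction, including towards no difference.

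**Working it through.** The plan gives no figure on this point, and no sample size or error rate depends on it. The check is a comparison of sections.

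1. **Are these the same calls?** Both sections place them at three and six months post intervention, and both collect visits to incontinence-related professionals. Nothing suggests two parallel sets of calls.

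2. **Are the two labels one role?** No. Trial management lists them separately: "The PI, the evaluators, physiotherapists, research assistant, and the Sherbrooke and Montreal coordinators conduct conference calls or face-to-face meetings". The Adherence list also keeps roles apart. It names the physiotherapist in items (1) and (2), a research assistant for appointment reminders in item (4), and evaluators in item (5).

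3. **Who are the evaluators?** The Recruitment section gives the on-site eligibility evaluation to the evaluator. The section on that evaluation says it is done by a physiotherapist. The Blinding section refers to physiotherapists who carry out outcome evaluations. Together these point to the evaluators being the blinded assessors, although the article never defines the term.

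4. **Is the research assistant blinded?** No. Under Intervention allocation, the research assistant in each centre obtains the allocation and tells the participant. Calls made by that role put no blinding at risk.

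5. **Could the questions reveal the arm?** Not by themselves. None of the listed topics asks about treatment format, and the home programme is common to both arms. However, the supervised treatments differ in ways that are easy to mention: a class of eight, or one-on-one sessions with an intravaginal biofeedback probe. Women are kept unaware of the other arm's treatment, so they cannot tell which remark would give theirs away.

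6. **When do the calls fall?** Assume that the 12-week programme (about 3 months) starts soon after randomization. The calls then come at about 3 + 3 = 6 and 3 + 6 = 9 months. The final assessment is 12 months after randomization, so they precede it by about 12 − 6 = 6 and 12 − 9 = 3 months. Waiting for a group to form would shorten these gaps.

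7. **Could the exposure recur?** The Adherence section also schedules an exercise-maintenance questionnaire at the 12-month evaluation. It does not say who administers it.

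**The case against.** The strongest reply is that this is loose role wording in a condensed article. Item (5) puts the calls in the passive and never says outright that evaluators place them. The only section that names a caller names the research assistant, which is compatible with blinding. By the time of the calls the supervised sessions are over, so adherence means keeping up exercises that both arms were taught. Women are also reminded at each assessment not to discuss treatment. The exposed outcomes are secondary, and the Data analysis section calls their analysis exploratory. Dynamometry is instrumented, and the weighed pad test remains as a further check.

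Much of this stands. A reader might infer that assessors were in fact unblinded, or that the muscle outcomes lose their value as a check. The documents support neither: they show a route to disclosure, not disclosure. A reader might also suspect the team meetings, but these are described only as monitoring study progress, with no mention of individual women's treatment.

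The reply does not remove the conflict. The sentence about evaluators directly follows the introduction of the calls inside item (5), so its natural reading is that evaluators collect the information during them. Site staff cannot follow both sections. An assessor who raises training adherence is at odds with the safeguard whether or not the arm comes out.

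**Conclusion.** The point holds as a contradiction between two sections, with an avoidable risk to assessor blinding. It rests on two readings that are natural but not explicit: that evaluators collect the item (5) information during the calls, and that they are the blinded outcome physiotherapists.

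The risk is confined to assessor-measured secondary outcomes at one year. The non-inferiority decision rests on the participant's seven-day diary and is not directly affected. The probability of unblinding and the size of any resulting bias cannot be derived from the document. The correction is more than clerical, because the choice of role decides whether the assessor discusses treatment with the women she or he will later examine.

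**What to change.** - In item (5) of the Adherence section, replace the evaluators with the research assistant already named under Costs related to interventions.
- State that adherence, consultation and co-treatment data, including the 12-month exercise-maintenance questionnaire, are collected by someone who does not assess outcomes.
- For calls already made, report who made them. If evaluators did, note this as a limit on the assessor-blinding claim. A wording change alone would then misdescribe conduct and could not restore blinding.

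The cost is small: each centre already has a research assistant who knows the allocation, so the change is one of wording and call assignment. The Trial status section reports 353 of 364 women recruited, so many calls may already be complete. The change can protect only the contacts still to come; for the rest, the remedy is disclosure.

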### Home PFMT program

Women in both groups are expected to perform PFM strengthening, endurance, and coordination exercises at home, five days a week, for the duration of the treatment [18, 22, 51, 55]. To support progression in the treatment, the home exercise program parallels the three phases in the treatment protocol with the gradual addition of increasingly difficult exercises every four weeks. To standardize home PFM exercises, each participant is given a PFM exercise diary describing the home PFMT exercises, in which they can record their adherence to the home program. Finally, all participants are asked to refrain from seeking other forms of treatment (such as medication or surgery) during the study.

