#### Data analysis

General analytical strategy: as opposed to conventional superiority trials, in non-inferiority trials per-protocol analysis is generally preferable to intention-to-treat (ITT) analysis, because the postulated hypothesis being tested assumes no difference between the two interventions [68]. Indeed, in non-inferiority trials, a “conservative” approach relies on a per-protocol analysis, which maximizes the probability of finding a statistically significant difference between the two groups, i.e. of rejecting the hypothesis that has motivated the trial. Moreover, the ITT approach includes all individuals who were initially randomized, regardless of their adherence, and thus may dilute, or even mask, the true difference between the interventions in the case of non-adherence or losses to follow-up [59]. In the extreme, if most participants do not adhere to the assigned intervention or fail to complete the follow-up assessment, the ITT analysis will automatically show no difference. To prevent such paradoxes, our main analysis will rely on the per-protocol approach, i.e. include only participants who will have completed the one-year assessment. On the other hand, because of its popularity, we will use the ITT approach in “sensitivity analyses,” as recommended by the CONSORT guidelines for non-inferiority trials [68]. Furthermore, our analyses will focus on (primary or secondary) outcomes at one year. Because all primary and secondary outcomes are measured on continuous scales, the methods outlined below for the analyses of the primary outcome will also apply to all secondary outcomes. However, the analysis of secondary outcomes will be exploratory in nature and some (e.g. for PFM function) may have more limited statistical power.

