Analyses for the primary outcome at one year (and secondary outcomes): The primary analysis will test our main hypothesis that group-based classes are not inferior to individualized treatment with respect to the primary outcome of relative (%) reduction in the number of leakages at one year post randomization. (For all outcomes, the analyses outlined below will be repeated using data on post-intervention assessment.) As recommended for non-inferiority trials, the hypothesis of non-inferiority will be accepted if, and only if, the upper bound of the two-tailed (1-2α) 95% CI (corresponding to a conservative Type I error of 0.025 for the one-tailed independent-group t-test) for the mean difference (in % reduction) excludes the non-inferiority threshold [68], set at 10% difference. This basic analysis will be extended to multivariable analyses. Specifically, two multivariable linear models, of increasing complexity, will be used to adjust the estimated difference between the % reduction at one year in the two groups for, respectively, (1) only the two stratification variables (center and type of UI), as well as the baseline number of UI episodes (to account for regression to the mean phenomenon); and (2) (if necessary) in addition to variables in model (1): any variable, for which a clinically important imbalance between the two arms is revealed by descriptive analyses (see above). In both models, the two-way interactions between the trial arm and (a) center and (b) UI type, will be tested using 1-df model-based F-tests to verify if the difference between the effects of the two interventions depend on either of those stratification variables. In the case of a statistically significant interaction (*p* < 0.05 for the F-test), the intervention effects will be estimated and tested separately in the respective subgroups [79]. The results of multivariable linear regression analyses will be summarized in terms of adjusted mean difference between the outcomes in the two trial arms, together with the 95% model-based CIs. In sensitivity analyses for primary and secondary outcomes at one year, ITT analyses will be conducted, using the same statistical methods.

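### The per-protocol set is defined only by one-year completion, so women who took other incontinence treatment stay in the primary non-inferiority comparison and no stated efficacy analysis takes account of it

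*Protocol article*

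**What the plan says.** All places are in the protocol article.

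- **Home PFMT program:** "all participants are asked to refrain from seeking other forms of treatment (such as medication or surgery) during the study".
- **Adherence:** calls are made at three and six months post intervention. On what the evaluators ask: "They also verify if medications have been prescribed, surgery conducted, and if there are any other health problems likely to influence UI". They also ask about visits to medical professionals for incontinence. **Costs related to interventions** uses those visits for costing.
- **Data analysis:** "our main analysis will rely on the per-protocol approach, i.e. include only participants who will have completed the one-year assessment". No other condition for belonging to the set is given. The reason offered is that intention-to-treat may dilute or mask a real difference between the interventions.
- **Primary outcome measure:** percent reduction in leakage episodes on the seven-day diary at one year.
- **Data analysis, primary outcome:** non-inferiority is accepted if the upper limit of the 95% CI "excludes the non-inferiority threshold [68], set at 10% difference". The adjusted models add the stratification factors, baseline episodes and any variable found imbalanced between arms in the descriptive comparison. Intention-to-treat is a sensitivity analysis with the same methods. All analyses are repeated on the post-intervention assessment.

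**The concern.** The 12-week programme ends about 40 weeks (52 − 12), or roughly nine months, before the one-year diary. A woman who still leaks has time to obtain a drug or surgery. She may have attended every session and every visit, so this is separate from attendance and from missing data.

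Taking such treatment departs from what participants were asked to do, yet the stated per-protocol rule keeps her in. Her one-year diary then reflects the assigned format plus the other treatment. If the group format were really worse, its women would have more reason to look elsewhere, and their later improvement would be credited to group training. That pulls the arms together in the very situation a non-inferiority test must guard against. Intention-to-treat with the same methods keeps the same women, so the two planned one-year analyses could agree without either addressing the problem.

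**Working it through.** **Inputs from the article**

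- Type I error: the two-sided 95% CI, "which corresponds to a stringent one-tailed type I error rate of α = 0.025"
- Power: "we estimated the sample size needed to ensure high (90%) power to demonstrate the non-inferiority of the group-based intervention"
- Margin: 10 points, individual minus group
- True difference for planning: "we assume that the true difference between the mean reductions (%) achieved by the two interventions will be zero"
- SD: "Accordingly, we assumed SD = 27% in our calculations"
- Evaluable size: 155 per group, 310 in total; 364 recruited to allow for 15% attrition

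**The plan's own figure**

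Normal approximation: n = 2 × (1.96 + 1.2816)² × 27² / 10² = 153.2, so 154 per arm. With the noncentral t distribution, 154 per arm gives power 0.8997 and 155 gives 0.9015, so the stated 155 reproduces. For attrition, 310 / 0.85 = 364.7, against the stated 364 (364 × 0.85 = 309.4). The design figures are sound.

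**Precision**

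SE = 27 × √(2/155) = 3.07. The CI half-width is 1.968 × 3.07 = 6.03 points.

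**Effect of other treatment**

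Let e be the proportion given other treatment in the group arm minus that in the individual arm. Let g be the extra percent reduction such treatment gives each treated woman, taken as equal in both arms. Then

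expected observed difference = true difference − e × g

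and approximately

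P(non-inferiority declared) = Φ((10 − observed difference − 6.03) / 3.07).

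Example: true difference 10, e = 0.05, g = 50. The observed difference is 10 − 2.5 = 7.5, and Φ((2.5 − 6.03)/3.07) = Φ(−1.15) ≈ 0.125. The noncentral t gives 0.126.

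The article gives neither e nor g, so both are assumptions and a range is shown. The true difference is set at the margin, where the nominal rate is 2.5%. SD is held at 27. Cells give the expected observed difference and the probability of declaring non-inferiority (noncentral t).

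| Excess in group arm | Gain 30 | Gain 50 | Gain 70 |
|---|---|---|---|
| 0 points | 10.0; 2.5% | 10.0; 2.5% | 10.0; 2.5% |
| 2 points | 9.4; 3.9% | 9.0; 5.1% | 8.6; 6.6% |
| 5 points | 8.5; 7.1% | 7.5; 12.6% | 6.5; 20.5% |
| 10 points | 7.0; 16.2% | 5.0; 36.9% | 3.0; 62.4% |

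Only the difference between arms matters in this model. Equal use with equal gain (for example 5% in both arms) leaves 2.5%. More use in the individual arm makes e negative and moves the result against non-inferiority.

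If the true deficit is well beyond the margin, the risk is much smaller. At 15 points, a 5-point excess gives 0.1% to 0.7%, and a 10-point excess gives 0.5% to 9.5%.

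**The case against.** **The article does not say that a diary completed after other treatment is used as recorded.** It fixes who is included, not how such an outcome is valued, and the full protocol or analysis plan may say more. That stands, and as-recorded use is an inference from the absence of any other stated rule. What remains is that the article itself defines the per-protocol set, and does so in a way that conflicts with its own reason for choosing it.

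**An existing analysis is largely free of the problem.** The post-intervention assessment comes one to two weeks after treatment ends, and all analyses are repeated on it. A deficit present by then would largely show there. This stands, but it cannot answer the one-year question, which is the primary one.

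**The plan does not predict that women will seek other treatment.** A reader might infer this from the calls, but asking is monitoring and no rate is given. Visits are also put to use, in the cost analysis. Only the efficacy analyses make no stated use of the call data.

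**A large error rate is easy to produce.** A 5-point excess with a rise from 30% to 95% reduction in each treated woman (a 65-point gain) gives a 3.25-point shift and about 18% false acceptance. The arithmetic is right, but neither input is in the document and the gain lies near the top of the range above, so it should not serve as the headline.

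**Analysing outcomes whatever other treatment was taken is a legitimate choice,** given objectives that include sustainability and one-year cost-effectiveness. That also stands. Making a 0% score the primary rule could over-correct. If such women would have shown 30% without other treatment, a 5-point excess moves the difference 0.05 × 30 = 1.5 points against the group arm. Power at a true difference of zero then falls from about 90% to Φ((10 − 1.5 − 6.03)/3.07) ≈ 79%, with SD held at 27.

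**Conclusion.** The point holds in a limited form. The stated per-protocol rule retains women who took the treatments they were asked to avoid, no stated efficacy analysis takes account of this, and the intention-to-treat sensitivity analysis shares the gap. The rule therefore does not deliver the protection for which the article chose it.

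The size is unknown. At a true deficit equal to the margin, false acceptance would be about 4–7% for an assumed 2-point excess in the group arm and about 7–20% for a 5-point excess, against 2.5%. These figures rest on assumed rates, gains of 30 to 70 points, equal gain in both arms and an unchanged SD.

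A reader might conclude that the trial is biased toward non-inferiority or will hide inferiority. The document does not support that: the direction depends on which arm uses more other treatment, equal use with equal gain gives no shift, and the request to refrain may keep use low. The supportable statement is that the one-year result could be affected and that the planned one-year analyses would not show it. It deserves correction before unblinding but does not undermine the design.

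**What to change.** Before unblinding:

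1. Flag every woman who had non-study treatment for incontinence (medication, surgery or physiotherapy) between randomisation and the one-year diary. Use the call data, and put the same questions at the one-year visit. The last call is about three months before that diary, and non-study physiotherapy is not among the items listed for the calls.
2. Report the number flagged by arm and type of treatment.
3. Keep the as-recorded analysis and add a pre-specified analysis of the primary outcome in which flagged women in both arms are scored as non-responders (for example 0% reduction) or by another stated rule. Claim non-inferiority firmly only if the two agree.
4. Apply the same pair of analyses to the model for response, defined as at least a 50% reduction.
5. Describe the per-protocol set accurately: either call it a one-year completers' set or state how other treatment bears on membership.

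The cost is a few added questions and one more analysis. That analysis will have a somewhat lower mean reduction, a larger SD and some loss of power. Neither the sample size nor participants' care changes.
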